#### **M. Manufacture and Distribution of Study Medications; The MEMS System**

The study medications, including all prenatal vitamins, the vitamin D tablets, and the placebo tablets will be manufactured by Tishcon Corp. Founded in 1976, Tishcon Corp. ([www.tishcon.com](http://www.tishcon.com)) is a leading manufacturer and marketer of vitamins, related dietary and herbal supplements, and private label non-prescription (OTC) pharmaceuticals in tablet, hard gelatin capsule, soft gelatin capsule and powder dosage forms. Tishcon is one of 12 soft gelatin capsule manufacturers in the United States. The pills and capsules will be sent in bulk from Tishcon to the DCC. The DCC will contract with the Brigham and Women's Hospital Pharmacy to package and label the pills in bottles with the MEMS caps. Once packaged and labeled with Study ID numbers, the pill bottles will be shipped to the respective Clinical Centers. Random pills from each lot will be sent to [name] lab where the vitamin D amount will be quantified for quality purposes. Each participant will receive 2 bottles – one bottle will contain the standard prenatal vitamins with 400 IU vitamin D, and will be labeled accordingly, and the other bottle will contain the intervention pill containing 4,000 IU vitamin D or a placebo.

**The MEMS System.** The MEMS® - Medication Events Monitoring Systems is a pill bottle equipped with special cap that includes an electronic microchip that stores the date and time of each opening of bottle. The MEMS monitors are drug packages with integral electronic micro circuitry designed to compile the dosing histories of ambulatory patients' prescribed medications. Each monitor consists of a conventional medicine bottle fitted with a special closure that records the time and date of each opening and closing of the container through integrated microcircuitry. The MEMS® stores up to 3800 medication events in non-volatile

EEPROM memory, allows wireless data transfer, fits standard pharmacy bottles 38mm-400, 42mm-400, and 45mm-400 thread closure, provides 36 months battery life, and is water-resistant and CE marked. Monitors are designed to be used by one patient with one drug. A Reader allows transferring the dose timing data from the MEMS to a MS-Windows based computer. The MEMS monitors have demonstrated reliability and validity and have been widely used with great success in clinical trial research, including NHLBI sponsored studies in the Childhood Asthma Research and Education Network and asthma clinical research sponsored by industry. The MEMS® - Medication Events Monitoring Systems is manufactured by Aardex LTD (<http://www.aardexgroup.com>) with a subsidiary in California for ease of ordering.

Data from the MEMS system will be downloaded monthly. The data from the pre-natal follow-up visits will be used to provide feedback to the participant, reinforcing those subjects with good adherence and providing extra teaching and encouragement for those with suboptimal adherence. These data can be used to derive a summary adherence measure that can be used as a covariate in our analyses and also for secondary analyses that exclude any women who have taken less than 50% of the prescribed study medication.

## **N. Statistical considerations**

### **N.1. Overview**

This is a randomized, double blinded, multi-center, placebo controlled, clinical trial of prenatal vitamin exposure as a preventive measure to reduce the risk of asthma and recurrent wheeze in childhood. There will be approximately 870 pregnant women enrolled, targeting an evaluable study population of 660 women randomized to Vitamin D supplementation of 4400 IU or 400 IU (standard prenatal supplementation). The treatment arms will be balanced (approximately n=300 in each arm, with some fluctuation possible owing to differential miscarriage or loss to follow-up, both expected to be completely at random). The primary outcome is doctor-diagnosed asthma and recurrent wheeze at 3 years of age. Secondary outcomes include allergy, doctor's diagnosis of eczema, and lower respiratory infection (LRI), at three years of age. The primary interpretive paradigm for analysis of this study is intent to treat.

### **N.2 Analytic plan**

All analyses to be described will occur in a framework of continuous quality assurance and verification. Preliminary statistical analysis will be used to describe the univariate distributions of key measures of interest to detect outliers or data anomalies that need to be addressed by data editing or sequestration of doubtful entries. Additionally, these analyses will examine whether any important risk factors for childhood asthma are imbalanced across treatment arm, as well as assess whether differential loss to follow-up is present across treatment groups. Detailed blinded codebooks will be provided to investigators as data accumulate to facilitate efficient substantive verification of basic distributional summaries and joint distributions of measured factors.

#### **N.2.a. Plan for Specific Aim 1**

For this analysis, our N will be 800, since most of the dropouts will be expected to occur after delivery. Thus, the expected drop in N due to the 8% miscarriage rate was applied. We will test the hypothesis that the dose of 4,000 IU per day is sufficient to get 90% of the women to a sufficient level of 25(OH)D of at least 30 ng/ml, primarily using a logistic regression model, with randomization group (i.e. intervention group vs. usual care) as the independent variable. The dependent variable will be 25(OH)D level at delivery. We will adjust our analyses for other covariates that may affect 25(OH)D level, such as sun exposure (from the SmartProbe and the sun exposure questionnaire), age, and diet (calculated vitamin D intakes from dietary sources).

#### **N.2.b. Plan for Specific Aim 2**

The hypothesis that the incidence of asthma and recurrent wheeze at age three years is reduced in the high-dose Vitamin D supplementation group will be tested using logistic

regression, allowing for fixed effects of center. Additional analyses will consider the modification of vitamin D exposure effects by maternal and child demographic/behavioral factors such as maternal age, BMI and weight gain during pregnancy, maternal history of asthma/allergy, and other factors potentially associated with asthma and/or Vitamin D exposure. The variables to be considered are summarized in Table 3. For variables that are measured post-natally, recall bias is a potential confounder among parents of infants diagnosed with asthma. However, the prospective nature of the data collection should limit the extent of this and other potential sources of bias. Due to the design of this clinical trial, we expect that the randomization process will distribute these variables equally between the intervention and control groups. However, we will check the distribution of these variables prior to conducting the analyses, and will adjust for variables that may be unevenly distributed across treatment and control groups.

**Table 3. Information on selected potential confounders of the relationship between 25(OH)D levels and asthma/recurrent wheeze in 3-yr old children**

|                                  |                                                                                 |
|----------------------------------|---------------------------------------------------------------------------------|
| Prenatal variables               | Socioeconomic status                                                            |
|                                  | Maternal diet                                                                   |
|                                  | Maternal sun exposure behavior                                                  |
|                                  | Maternal age and parity                                                         |
|                                  | Maternal history of asthma and allergies                                        |
|                                  | Maternal pre-pregnancy BMI and weight gain in pregnancy                         |
|                                  | Maternal medication use in pregnancy (antibiotics, acetaminophen, NSAIDs, etc.) |
|                                  | Pregnancy complications (e.g. gestational diabetes, pre-eclampsia)              |
| Delivery variables               | Gestational age                                                                 |
|                                  | Mode of delivery (caesarian section, normal vaginal delivery)                   |
|                                  | Birthweight, length, head circumference                                         |
|                                  | Oxygen use                                                                      |
|                                  | Need for NICU stay                                                              |
| Postpartum and infancy variables | Breastfeeding or bottlefeeding                                                  |
|                                  | Type of formula                                                                 |
|                                  | Timing and type of solid food introduction                                      |
|                                  | Daycare, including timing of and type of daycare (home vs institution)          |
|                                  | Pets in the home                                                                |
|                                  | Other siblings in the home (gender and number)                                  |
|                                  | Smoking in the home                                                             |
|                                  | Childhood diet                                                                  |
|                                  | Sun exposure behaviors in the child                                             |

Letting  $M_i$  be an indicator function for the primary endpoint, asthma, for the  $i^{\text{th}}$  subject, the model is:

$$\text{logit } \Pr(M_i = 1 \mid x_i, a_i) = \alpha + \beta x_i + \gamma_1 a_{1,i} + \gamma_2 a_{2,i}$$

where  $x_i$  denotes an indicator function for level of vitamin D supplementation (0=400 IU, 1=4400 IU) in the  $i^{\text{th}}$  subject, while  $a_{1,i}$  and  $a_{2,i}$  are indicator functions for study center. The specific aim for this outcome tests the hypothesis that  $\beta=0$ , asthma and recurrent wheeze incidence do not significantly differ across treatment groups, after adjusting for the potential effects of study center heterogeneity.

To assess modification of vitamin D exposure levels by other demographic and/or behavioral variables, the model is:

$$\text{logit } \Pr(M_i = 1 \mid x_i, a_i) = \alpha + \beta x_i + \gamma_1 a_{1,i} + \gamma_2 a_{2,i} + \sum_k \delta_k z_{ki} + \sum_k \eta_k x_i z_{ki}$$

where  $z_{ki}$  represents the  $k$  measured covariates for each subject, and the other variables are as described above. This model addresses two hypotheses. First, main effects testing for behavioral/demographic covariates (Table 9), or the hypothesis that  $\delta_k=0$ , will be used to examine whether maternal age, BMI, or other factors predict asthma and recurrent wheeze risk at age 3. More importantly, inclusion of any significant main effects will adjust for any distributional imbalances of these factors across the Vitamin D supplemented and placebo groups. Second, this model tests the hypothesis that  $\eta_k=0$ , or whether any maternal, child, or demographic/behavioral covariates modify the relationship between vitamin D intake and our primary outcome. To obtain a parsimonious model and limit multiple testing, only covariates with significant main effects and strong biologic plausibility for an exposure-dependent impact on asthma/recurrent wheeze risk will be considered for interaction testing with Vitamin D supplementation status. For example, only the prenatal and some delivery variables (e.g., gestational age, birthweight, length) listed in Table 9 will be considered, as the factors modifying the impact of Vitamin D supplementation on asthma and/or recurrent wheeze should occur temporally (i.e. in utero).

#### **N.2.b.1. Interim Analyses for Specific Aim 2**

For the primary aim of asthma and recurrent wheeze, we have developed an interim analysis plan to monitor this composite endpoint over the three years of subject follow-up. This sequential monitoring plan consists of two interim analyses (conducted at year 3 month 12 or when all first year study visit data are available and year 4 month 12/when all first and second year visit data are available), and a final analysis at the end of year 5, when the three-year follow-up has been completed on all subjects. For maximum flexibility in the analysis, we will use a Lan-Demets alpha spending function with O'Brien-Fleming bounds. While the power simulations described in section O.2 use stopping boundaries that are designed for 3 'looks' over the study period, the Lan-DeMets procedure provides a spending function approach which does not require pre-specification of the frequency or timing of interim looks. This can be advantageous if the timing of data collection varies or if the need for more frequent monitoring arises. Conservative O'Brien-Fleming bounds are used to preserve most of the type-I error for the final analysis. The specific boundaries for the interim analyses are provided in section O.2. Only the primary endpoint of asthma and/or recurrent wheeze will be monitored sequentially. If the boundaries are crossed at either the first or second year analyses, results will be immediately reported and the study will be stopped.

#### **N.2.c Plan for Specific Aim 3**

Incidence of allergy, doctor's diagnosis of eczema, and lower respiratory tract infection (LRI) at age 3 will be individually assessed. Like asthma and recurrent wheeze, two of the three secondary outcomes are dichotomous endpoints, and will be analyzed using logistic regression. For allergy, logistic regression will be used for specific IgE and linear regression will be used for log transformed total serum IgE level. Both a primary analysis of the relationship between Vitamin D and the secondary outcome of interest will be conducted, as well as additional analyses including demographic and environmental risk factors for allergy, eczema, and LRI. The primary analysis, as well as additional analyses testing main demographic/behavioral effects and effect modification, will be conducted along the lines of analyses described for Specific Aim 2. The covariates to be considered for main effects and interaction analyses will be identical to those outlined for Specific Aim 2.

#### **N.2.d. Plan for Specific Aim 4**

This specific aim investigates the immediate and long-term impact of vitamin D supplementation on circulating 25(OH)D blood levels. The immediate impact of Vitamin D on 25(OH)D will be assessed through maternal plasma and cord blood measurements taken at

delivery. The long-term influence will be examined via longitudinal analyses using children's blood measurements obtained at ages 1 and 3.

The hypotheses that 25(OH)D levels in maternal plasma and cord blood will be higher in the 4400 IU group will be tested using standard linear regression. If necessary, 25(OH)D levels will be transformed to meet the distributional requirements for the analysis. The 25(OH)D levels in maternal plasma and cord blood will be treated as separate outcomes, although both testing procedures for each analysis will be similar and are described jointly below. As with specific aims 1 and 2, the primary analysis will examine the relationship between 25(OH)D and Vitamin D levels, while the secondary analysis will include other important demographic and environmental factors related to 25(OH)D levels, such as climate and dietary vitamin D intake, testing for main effects and effect modification for these factors.

Letting  $y_i$  denote the 25(OH)D levels for each subject (as measured in mother's plasma for the first hypothesis, and cord blood for the second hypothesis), the model for the primary analysis is:

$$y_i = \alpha + \beta x_i + \gamma_1 a_{1,i} + \gamma_2 a_{2,i} + \varepsilon_i$$

where the covariates and parameters are as defined in Specific Aim 1. However, Specific Aim 3 tests the hypothesis that  $\beta=0$ , 25(OH)D levels do not significantly differ across the Vitamin D supplemented and control groups. All relevant covariates listed in Table 3 will be considered for the final model. For example, covariates measured post-natally would not be considered for inclusion in the analysis of maternal plasma or cord blood at delivery. Additionally, factors known to be directly associated with OH(25)D levels (i.e. sun exposure behavior, diet, ethnicity), will be included in the final model even if they are not statistically significant predictors of circulating vitamin D levels.

To assess modification of 25(OH)D levels by other demographic and behavioral variables, the model is:

$$y_i = \alpha + \beta x_i + \gamma_1 a_{1,i} + \gamma_2 a_{2,i} + \sum_k \delta_k z_{ki} + \sum_k \eta_k x_i z_{ki} + \varepsilon_i$$

where the parameters are as defined in Specific Aim 1. The  $k$  measured covariates for these analyses will be environmental, maternal, and child factors specific to 25(OH)D levels, such as sun exposure behavior, dietary intake of Vitamin D, and ethnicity. Additionally, any relevant covariates from Table 9 demonstrating main effects that have biologically plausible interactions with Vitamin D supplementation will be tested for effect modification. For both models, it is assumed that  $\varepsilon_i \sim N(0, \sigma^2)$ . The hypothesis that  $\delta_k=0$  will be used to examine whether any of these factors predict 25(OH)D levels, and the results will be used to adjust for any distributional imbalances of these factors across Vitamin D supplementation groups. As with the previous specific aims, we will also tests for effect modification via the hypothesis that  $\eta_k=0$ , or whether any maternal, child, or demographic/environmental covariates modify the relationship between vitamin D intake and circulating 25(OH)D levels in mother's plasma or cord blood. Additionally, we will follow the guidelines outlined in Specific Aim 2 to obtain the most parsimonious model.

The hypothesis that 25(OH)D levels in the child's blood will be higher in the 4400 IU group at birth, age 1 and age 3 will be tested using a repeated measures analysis framework such as generalized estimating equations.

### N.3 Multiple comparisons.

All pre-specified hypotheses will be tested individually at the 0.05 level of significance, using a conservative two-sided alternative hypothesis (even when the stated hypothesis is one-sided). More specifically, the primary and secondary hypotheses of Vitamin D supplementation and Asthma/Recurrent Wheeze, Allergy/Excema/LRI, will not be adjusted for multiple comparisons, since they have been defined a priori and are limited in scope. Additionally, an interim analysis plan has been developed for the primary outcome to adjust for the number of times (3) asthma and/or recurrent wheeze will be analyzed over the study period. Since

25(OH)D status is being examined in 5 separate analyses (maternal plasma at 26-28 weeks, maternal plasma at delivery, cord blood at delivery, infant plasma at years 1 and 3), this analysis will be adjusted for 5 multiple comparisons (i.e., using Bonferroni correction). Finally, any findings with respect to interaction terms (i.e., exploring whether environmental and demographic covariates affect the relationship between Vitamin D supplementation and the outcome of interest) for any of the hypotheses will be adjusted (i.e., using FDR methodology) for the number of models tested, and interaction testing will be limited to those defined in sections D.14.2a-c, in order to limit the potential for spurious findings. Any serendipitous findings coming from exploratory analyses will be clearly reported as such, and test statistic p-values will be adjusted by the number of exploratory hypotheses considered (using FDR or another appropriate procedure for multiple comparisons adjustment).

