### P.3 Multiple comparisons.

All pre-specified hypotheses will be tested individually at the 0.05 level of significance, using a conservative two-sided alternative hypothesis (even when the stated hypothesis is one-sided). More specifically, the primary and secondary hypotheses of Vitamin D supplementation and Asthma/Recurrent Wheeze, Allergy/Eczema/LRI, will not be adjusted for multiple comparisons, since they have been defined a priori and are limited in scope. Additionally, an interim analysis plan has been developed for the primary outcome to adjust for the number of times (3) asthma and/or recurrent wheeze will be analyzed over the study period. Since 25(OH)D status is being examined in 5 separate analyses (maternal plasma at 26-28 weeks, maternal plasma at delivery, cord blood at delivery, infant plasma at years 1 and 3), this analysis will be adjusted for 5 multiple comparisons (i.e., using Bonferroni correction). Finally, any findings with respect to interaction terms (i.e., exploring whether environmental and demographic covariates affect the relationship between Vitamin D supplementation and the outcome of interest) for any of the hypotheses will be adjusted (i.e., using FDR methodology) for the number of models tested, and interaction testing will be limited to those defined in sections D.14.2a-c, in order to limit the potential for spurious findings. Any serendipitous findings coming from exploratory analyses will be clearly reported as such, and test statistic p-values will be adjusted by the number of exploratory hypotheses considered (using FDR or another appropriate procedure for multiple comparisons adjustment).

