**Table 6. Power to detect a 25-35% reduction in secondary outcomes for 870 subjects in a multi-site study, (effectively 660 patients, assuming an 8% miscarriage rate and 18% loss to follow-up)**

| Mean Incidence of secondary outcome in 400 IU group | Percent reduction in secondary outcome in 4400 IU group |            |            |
|------------------------------------------------------------|----------------------------------------------------------------|------------|------------|
|                                                            | 35%                                                     | 30% | 25% |
| 0.50                                                | 0.998                                                          | 0.982      | 0.913      |
| 0.45                                                | 0.992                                                          | 0.958      | 0.858      |
| 0.40                                                | 0.973                                                          | 0.906      | 0.779      |
| 0.35                                                | 0.936                                                          | 0.845      | 0.691      |
| 0.30                                                | 0.890                                                          | 0.736      | 0.608      |
| 0.25                                                | 0.795                                                          | 0.654      | 0.531      |

**Q.4. Power for Specific Aim 4.** The research to date on the impact of vitamin D supplementation on 25(OH)D is presented in Table 1. As noted in the table, only 4 studies have been conducted on pregnant women, all had fewer than 100 subjects, and the maximum daily dose for these studies was 1,600 IU. The only data available on 25(OH)D status in the supplementation ranges we are proposing has been provided by [name] (unpublished data, see section III). In a study of 347 pregnant women (African Americans, Hispanic,

and Caucasians) on either 4000 IU (supplemented) or 400 IU (control) of Vitamin D daily, the maternal plasma 25(OH) D levels were 115 nmol/L in supplemented subjects, and 80 nmol/L in controls after 8 months of supplementation, an overall difference of 35 nmol/L. The estimated standard deviation for 25(OH)D levels in these ranges is 40.

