Based on the observed differences/variation in 25(OH)D levels, we used simulation studies to estimate the power to detect a mean difference of 7.5 – 37 nmol/L across the supplemented and control groups in maternal plasma at 26-28 weeks, as well as maternal plasma and cord blood at delivery, using an estimated standard deviation of 40. We anticipate that the difference in 25(OH)D levels in maternal plasma across treatment groups will be less

pronounced at the 26-28 week measurement period (e.g., 12.5 – 25 nmol/L), and we do not expect to observe a significant difference by supplementation status in circulating vitamin D in infants at 1 and 3 years of age, since no post-natal treatment intervention is planned. The simulations were generated in a similar manner to method described for Specific Aim 2, except that linear regression (rather than logistic) was used to model the relationship between circulating vitamin D and vitamin D supplementation status. Study heterogeneity was incorporated into the model by allowing 25(OH)D levels to vary by 25 nmol/L across study sites. Since this phenotype will be measured five times throughout the study period, the power was defined as the proportion of replicates with a Wald test statistic (i.e., testing the null hypothesis that the coefficient for vitamin D supplementation status is 0) 2-sided p-value was less than 0.01 (0.05/5). Additionally, this specific aim will include 2 interim and a final analysis, which will be identical to the procedure outlines for specific aim 2. While the power estimates below do not directly incorporate the interim looks, we feel that the power reduction will be modest. The results are shown in Table 7.

**Table 7. Power to detect a 7.5 – 37 nmol/L difference in 25(OH)D for 870 subjects in a multi-site study, (effectively 660 patients, assuming an 8% miscarriage rate and 18% loss to follow-up).**

| Mean change in 25(OH)D levels in 4400 IU group (nmol/L) | Power |
|---------------------------------------------------------|-------|
| 7.5                                                     | 0.444 |
| 12.5                                                    | 0.925 |
| 25                                                      | 0.999 |
| 37                                                      | 0.999 |

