For a mean difference greater than 7.5 nmol/L, we anticipate having excellent power to detect a difference in 25(OH)D status across treatment groups. This difference of at least this magnitude should be observed in both maternal plasma measurements and cord blood, given the preliminary data (a difference of 35 nmol/L in maternal plasma) provided by [name]. To ensure that the results were not affected by incorporating an effect for study center, the simulations were conducted assuming homogenous effects across study sites. The power estimates were within 1.5% of those provided above, and are likely due to variation in estimates via simulation. Therefore, we are confident that we have excellent power to achieve this specific aim.

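### The 25(OH)D comparisons are adjusted by single-step Bonferroni at 0.01; Holm's step-down procedure over the samples actually scheduled keeps the same family-wise 0.05 with more power

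*Supplement*

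**What the plan says.** All references are to the current protocol.

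- **P.3 (Multiple comparisons)** counts five 25(OH)D analyses: "maternal plasma at 26-28 weeks, maternal plasma at delivery, cord blood at delivery, infant plasma at years 1 and 3". It then says that "this analysis will be adjusted for 5 multiple comparisons (i.e., using Bonferroni correction").
- **Q.4 (Power for Specific Aim 4)** applies this as a fixed threshold: success means that the "2-sided p-value was less than 0.01 (0.05/5"). Table 7 is computed at that level, "using an estimated standard deviation of 40" and a sample that is "effectively 660 patients, assuming an 8% miscarriage rate and 18% loss to follow-up".
- **Expected effects (Q.4).** Maternal plasma after 8 months of supplementation: "an overall difference of 35 nmol/L". Earlier in pregnancy the contrast is expected to be less "pronounced at the 26-28 week measurement period (e.g., 12.5 – 25 nmol/L"). Cord blood has no figure of its own. After naming 7.5 nmol/L, the text says only: "This difference of at least this magnitude should be observed in both maternal plasma measurements and cord blood". For children at 1 and 3 years, Q.4 expects no significant difference, because nothing is given after birth as part of the randomized intervention.
- **P.2.d (Aim 4)** tests the child's levels at birth, age 1 and age 3 within a repeated-measures framework such as GEE.
- **VI.F and Table 2** schedule maternal blood at randomization, 32–38 weeks and one year after delivery, cord blood at delivery, and child blood at 1 and 3 years.

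No step-down, ordered or gatekeeping procedure appears in the protocol, and the Analysis Plan addendum does not change the adjustment.

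**The concern.** Single-step Bonferroni holds every comparison to 0.05/5, however many of the others have already been rejected. In this family the maternal comparisons are expected to be large and need little of the allowance. The child comparisons at 1 and 3 years are where a small difference, if there is one, would be hard to detect. They belong to a stated aim: Aim 4 asks about offspring vitamin D status at those ages, and P.2.d states the directional hypothesis. Holm's procedure gives the same family-wise guarantee without assumptions about dependence and relaxes the level for the remaining tests as others are rejected. At stake is sensitivity on a secondary aim. Type I error is controlled either way.

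**Working it through.** **Inputs.** SD 40 and 330 per arm (660/2), two-sided level 0.01, from Q.4 and Table 7. Maternal effects of 35 and 12.5–25 nmol/L, from Q.4. The documents give no child effect and no cord figure beyond about 7.5 nmol/L, so values for those are assumptions and are varied below.

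**1. Reproduce Table 7.** SE = 40·√(2/330) = 3.114. Power ≈ Φ(δ/SE − z), with z = 2.576 at level 0.01.

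- δ = 7.5: 7.5/3.114 = 2.41; power 0.434 (Table 7: 0.444)
- δ = 12.5: 12.5/3.114 = 4.01; power 0.925 (Table 7: 0.925)
- δ = 25 and 37: above 0.999 (Table 7: 0.999)

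The plan's figures are reproduced to within simulation error.

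**2. Levels under Holm, five tests.** The ordered p-values meet 0.05/5 = 0.01, 0.05/4 = 0.0125, 0.05/3 = 0.0167, 0.05/2 = 0.025 and 0.05. If the three maternal and cord nulls are rejected first, the smaller child p-value is tested at 0.025. If that is rejected, the other is tested at 0.05.

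**3. Power of one child comparison at each level (assumed effects).**

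| δ (nmol/L) | 0.01 | 0.0125 | 0.025 | 0.05 |
|---|---|---|---|---|
| 5 | 0.166 | 0.186 | 0.262 | 0.362 |
| 7.5 | 0.434 | 0.464 | 0.566 | 0.673 |
| 10 | 0.737 | 0.762 | 0.834 | 0.895 |

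The difference detectable with 80% power is 10.6 nmol/L at 0.01, 9.6 at 0.025 and 8.7 at 0.05.

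**4. Whole procedure, simulated.** 200,000 replicates, correlation 0 and 0.5, child effect 7.5 nmol/L. Bonferroni power per child comparison is about 0.43 throughout.

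| 26–28 wk / delivery / cord (nmol/L) | All three rejected at 0.01 | Holm, effect at both ages | Holm, effect at one age |
|---|---|---|---|
| 25 / 35 / 35 | 1.00 | 0.62–0.63 | 0.57 |
| 12.5 / 35 / 25 | 0.92–0.93 | 0.62 | 0.57 |
| 12.5 / 35 / 12.5 | 0.86–0.87 | 0.62 | 0.56 |
| 12.5 / 35 / 7.5 | 0.40–0.43 | 0.58 | 0.54 |

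**5. Family that matches the current schedule.** With maternal 32–38 weeks, cord blood, child year 1 and child year 3, Bonferroni is 0.05/4 = 0.0125. With the first two set at 25 and 35 nmol/L (correlation 0.5) and 7.5 nmol/L at both ages, power per age is 0.46 (Bonferroni) against 0.62 (Holm).

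**6. No child effect.** The chance of at least one false child finding is about 0.02 under five-test Bonferroni. Under Holm it is 0.04–0.05 across the scenarios in step 4. As a check, two independent tests once the other three are rejected give 1 − 0.975² = 0.049. In the four-test family it is 0.023 against 0.046. Family-wise 0.05 holds in each case.

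**The case against.** Bonferroni is valid, prespecified, and applied consistently in P.3 and Table 7, so no inference would be wrong. The plan also does not rely on the child comparisons: Q.4 expects no significant difference at ages 1 and 3, and section IV offers 400 IU/day to infants taking less than 1000 ml of formula a day, whatever their arm. The child effects above are assumed, and SD 40 comes from maternal data. If the plan's expectation is right, Bonferroni gives fewer false child findings. Holm is also more than a change of word: P.2.d places the child measurements in one repeated-measures model, and the Aim 4 bounds need attention (see the fix).

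All of this stands, and it limits the point to efficiency. It does not restore an advantage to Bonferroni at family-wise 0.05: Holm meets the same guarantee and never rejects less.

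Two stronger readings are tempting. A reader might infer that three of the five comparisons succeed almost surely. Q.4 supports that for the 35 nmol/L maternal contrast and for the upper end at 26–28 weeks. Power at the lower end is 0.925, and cord blood has only the floor of about 7.5 nmol/L, at which all three succeed in only 0.40–0.43 of replicates. A reader might also infer that the trial loses power it was counting on. It does not, because Q.4 plans for no child effect.

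**Conclusion.** The point holds as an efficiency gain and not as a validity error. P.3 fixes a method that is less powerful than Holm at the same family-wise 0.05.

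Assuming 7.5 nmol/L at both ages, SD 40 and 330 children per arm, power per age rises from about 0.43 (five-test Bonferroni) or 0.46 (four-test) to about 0.58–0.62, depending on the maternal and cord effects. With an effect at one age only, it is at most about 0.57. Fewer child blood samples would lower all of these figures.

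The family of five is itself out of date: VI.F and Table 2 contain no maternal draw at 26–28 weeks or at delivery. This changes the Bonferroni level from 0.01 to 0.0125 but not the direction of the comparison.

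**What to change.** **P.3.** List the 25(OH)D comparisons that the current schedule supplies: maternal plasma at 32–38 weeks, cord blood, child year 1, child year 3. State that the two child contrasts come from the repeated-measures model in P.2.d. Test the four with Holm's step-down procedure at family-wise 0.05, applied once all p-values are available.

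**Align with VII.K and VII.L.** The Aim 4 bounds (|z| = 3.7103, 2.5114, 1.993) together spend about 0.05, and the last corresponds to a nominal two-sided p of 0.046, not 0.01. The final Aim 4 analysis is set for year 4 month 5, whereas the first 3-year visits are in year 5 month 5. The text should say how the looks and the step-down levels combine and when the family is closed.

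**Q.4.** Label the power in Table 7 as first-step (worst-case) power.

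**Cost.** A few sentences and no new data. There are two small downsides. Holm has no simple matching simultaneous intervals, although Bonferroni-level intervals can still be shown. If there is no child effect, the chance of a false child finding rises from about 0.02 to about 0.05, still within the family-wise limit.
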